#### Inclusion criteria

Inclusion criteria for patients with MCI are as follows: (1) patients aged 50–70 years, (2) patients meeting the Peterson diagnostic criteria for MCI, (3) duration of memory loss longer than 3 months, (4) educational level longer than 6 years, (5) a MoCA-K score < 23, (6) a CDR score of 0.5 and GDS grade 2–3, (7) a Modified Hachinski Ischemic Score (HIS) score ≤ 4, and (8) patients who voluntarily sign the informed consent form.

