### Sample size calculation

To assess the efficacy of the intervention, the minimal clinically important difference (MCID) of DST was considered. However, there was no well-established prior study to derive the MCID of DST. Thus, the effect size was calculated from a similar study examining acupuncture treatment for MCI.

The sample size is estimated based on the result from a previous study [29]. The mean difference in the DST score is assumed to be 0.87 and the standard deviation (SD) of that is assumed to be 0.89 between the acupuncture group and sham acupuncture group. Sample size calculation shows that a total of 44 patients is needed for 90% statistical power and 5% significance level. With an estimated dropout ratio of 10%, the necessary sample size is 50 patients (25 patients for each acupuncture group).

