Statistical comparisons of data on MRI outcomes will be performed differently. Voxel-wise generalized linear model (GLM) analysis will be performed to compare gray matter volumes within and between groups while controlling for age and sex. Statistical maps of comparisons in gray matter volumes will be corrected for multiple comparisons using the false discovery rate (FDR, *p* < 0.05). Similar to gray matter volumes, differences in brain responses to the WM task and functional connectivity from the resting state fMRI at baseline will be assessed between groups using the independent samples *t* test and voxel-wise GLM analysis (FSL, feat). fMRI metrics between baseline and post-treatment will be compared using the paired samples *t* test in a voxel-wise GLM. Age and sex will be added to the GLM as regressors of no interest. Correction for multiple comparisons of fMRI metrics will be performed using a corrected cluster-size threshold of *p* < 0.05. Statistical comparisons The DTI metric maps will be statistically compared within and between groups using a non-parametric permutation test with 5000 permutations. For multiple comparisons across voxels in DTI metric maps, family-wise error correction will be used with threshold-free cluster enhancement (Randomise, FSL). Whole-brain linear regression analyses will be performed to test association between metrics of cognitive function and changes in brain function and structure. This trial will enroll 50 patients with MCI and this could be a cohort with heterogeneous cognitive function. Thus, we will follow up the aforementioned analyses to evaluate brain function and structure in subgroups with different cognitive functions at baseline. We will divide patients with MCI into equal sample sizes of low-cognitive and high-cognitive function subgroups using the MoCA-K. We will compare between MRI outcomes for low-cognitive and high-cognitive function to test whether cognitive function affects brain function and structure groups, using the independent samples *t* test with identical multiple comparisons correction, as previously described.

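### Splitting baseline MoCA-K into equal low and high halves loses information and probably separates tied patients; a continuous regressor fits the GLM already planned

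*Protocol article*

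**What the plan says.** The closing part of Statistical analysis, on MRI outcomes, notes that the enrolled patients may vary in cognitive function and continues: "Thus, we will follow up the aforementioned analyses to evaluate brain function and structure in subgroups with different cognitive functions at baseline". The grouping rule is "We will divide patients with MCI into equal sample sizes of low-cognitive and high-cognitive function subgroups using the MoCA-K". The comparison and its purpose follow: "We will compare between MRI outcomes for low-cognitive and high-cognitive function to test whether cognitive function affects brain function and structure groups". The method is an independent samples t "test with identical multiple comparisons correction, as previously described".

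Three other statements bear on this:

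- Inclusion criteria require "a MoCA-K score < 23", so the score is capped at 22 in this sample.
- Sample size calculation states that "the necessary sample size is 50 patients (25 patients for each acupuncture group". If everyone is analysed, the halves are 25 and 25.
- Statistical analysis also plans a continuous analysis: "Whole-brain linear regression analyses will be performed to test association between metrics of cognitive function and changes in brain function and structure". It does not say that baseline MoCA-K is one of those metrics.

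The article gives no effect size or power for the low/high comparison.

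**The concern.** The variable, the cut and the test are all fixed in the article, so this is a stated choice and not a detail left to another document. Two features of the choice are weak.

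First, replacing a graded score by two labels treats everyone within a half as alike, and treats two patients on either side of the cut as being as different as the extremes. In a sample sized for a large effect on another outcome, the lost information is hard to spare.

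Second, exactly equal groups are hard to form from an integer score with a restricted range. When the patients ranked 25th and 26th share a score, someone must decide which of the tied patients counts as low and which as high. The cut-point is also a property of the recruited sample, so a low group here need not match a low group in another study.

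At stake are the sensitivity and reproducibility of one exploratory MRI analysis.

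**Working it through.** **The plan's own figure.** The only sample-size figure is for the DST. With difference 0.87, SD 0.89, two-sided 5% and 90% power, n per arm = 2 × (1.960 + 1.282)² × (0.89/0.87)² ≈ 22, or 44 in total. Then 44/0.90 = 48.9, so 49, or 50 with equal arms. The figure reproduces. It says nothing about the MoCA-K comparison, so everything below rests on labelled assumptions.

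**Information kept by a split at the median.** For a linear relation, the share kept is the squared correlation between the score and the half indicator, that is (half the gap between the two half-means)² divided by the variance of the score.

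| Assumed shape of score | Calculation | Kept | Lost |
|---|---|---|---|
| Normal | (√(2/π))² = 2/π | 64% | 36% |
| Uniform | 0.25² ÷ (1/12) | 75% | 25% |
| Exponential-shaped | (ln 2)² | 48% | 52% |

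Under the normal assumption, 50 × 0.637 = 31.8, so 50 patients carry the information of about 32, a loss of about 18.

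**Power for one test, no voxel-wise correction, n = 50.** Power = Φ(atanh(r) × √47 − 1.96), where √47 = 6.856. For the split, r is multiplied by √(2/π) = 0.798. The correlations are assumptions.

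- r = 0.4, continuous: 0.4236 × 6.856 − 1.96 = 0.94, power 83%.
- r = 0.4, split (r becomes 0.319): 0.3307 × 6.856 − 1.96 = 0.31, power 62%.
- r = 0.3, continuous: 0.3095 × 6.856 − 1.96 = 0.16, power 56%.
- r = 0.3, split (r becomes 0.239): 0.2441 × 6.856 − 1.96 = −0.29, power 39%.

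A simulation of the two tests (20,000 runs) agrees: 83% v 63% at 0.4 and 58% v 39% at 0.3. With 44 patients it gives 79% v 57% and 52% v 36%.

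**Ties.** The article gives no MoCA-K distribution. Samples of 50 were therefore drawn from six assumed distributions (mean 17 to 21, SD 2 to 4, rounded to integers, capped at 22). The 25th and 26th patients tied in 82% to 93% of samples, with roughly 6 to 12 patients sharing the cut value on average.

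**What an optional interaction test could show.** On the DST planning scale (SD 0.89, N = 50), the standard error of the acupuncture–sham difference is 0.89 × √(4/50) = 0.252. The standard error of the difference in that effect between two halves is 0.89 × √(16/50) = 0.503, twice as large. Power for an interaction of 0.87 is Φ(0.87/0.503 − 1.96) = Φ(−0.23), about 41%. An interaction of 0.503 × (1.960 + 0.842) = 1.41 would be needed for 80%.

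**The case against.** The strongest reply is that the low/high comparison addresses the question the article poses, whether cognition affects brain function and structure, and that this is a follow-up analysis on which no main conclusion depends. Both parts are right, and they limit the weight of the point. They do not make the split the better way to answer that question.

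A second reply is that the whole-brain regression already treats cognition continuously. This is a partial answer: it concerns changes in the brain, and it is not tied to baseline MoCA-K.

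A third is that the power figures are loosely grounded. That also stands: the correlations are assumed, the 64% depends on the shape of the score, and voxel-wise correction is ignored. The figures show the direction and rough size of the loss, not the power of the planned maps.

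A fourth is that a tie rule can be left to the analysis plan. So it can, but any such rule would still separate patients with identical scores, which a continuous regressor avoids.

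Two stronger readings are tempting and are not supported:

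- A reader might infer that the plan fails to test whether the acupuncture effect depends on baseline cognition. The article never promises that test; its stated reason is variation in cognition among the patients, not variation in treatment effect. What is fair to say is that a low/high difference must not be read as effect modification.
- A reader might infer that the comparison drops the age and sex adjustment. The section names t tests alongside, and as contrasts within, a GLM with age and sex as regressors, and presents this step as a follow-up of those analyses. Nothing says the covariates are removed.

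**Conclusion.** The point holds as a modest improvement to an exploratory analysis. The equal-halves split gives up about 36% of the information under a roughly normal score and a linear relation, and between 25% and 52% for the other two shapes considered. For one uncorrected test at n = 50 that is about 17 to 21 percentage points of power at assumed correlations of 0.3 to 0.4. Ties at the cut are likely but not certain, since the MoCA-K distribution in this sample is unknown. The absence of an arm-by-MoCA-K test is not an error. The DST analysis and the main MRI comparisons between arms do not depend on this choice.

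**What to change.** Replace the low/high t test by baseline MoCA-K as a continuous regressor in the voxel-wise GLM already planned, with age, sex and scanner or site as covariates (MRI scanning procedure describes a different scanner model at each hospital). Add arm when post-treatment or change maps are analysed. Keep the multiplicity corrections already stated, and use the low/high split for display only.

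If the team wants to look at effect modification, an arm × MoCA-K term on the change maps can be added, labelled exploratory and low-powered.

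The cost is wording only, with no new data. The model then assumes a linear relation, which should be checked, and a slope is slightly less simple to present than two group means.

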### Safety

Adverse events (AEs) will be recorded at each visit during the trial. Among the AEs, the following cases are defined as serious AEs (SAEs): (1) death or threat to life, (2) hospitalization (initial or prolonged), (3) disability or permanent damage, (4) congenital anomaly/birth defect, and (5) other important medical events. If SAEs occur, the principal investigator should notify the Sponsor within 24 h. If a participant reports an AE or SAE, the investigators evaluate whether the AEs or SAEs are related to the intervention. If required, appropriate medical management should be provided under the usual victims’ compensation principles. If the adverse event is too serious to continue the trial, the participant will be withdrawn. However, if the AE or SAE is probably not or definitely not related to the intervention and the harm is not serious, the participant will not be withdrawn.

The AEs and SAEs will be recorded for safety assessment. Given the safety of acupuncture, we did not pre-define a safety endpoint, as it was deemed unlikely that a large number of meaningful AEs would be observed.

### Data management

In this trial, all data will be recorded electronically. This may be done at the participating site where the data originated. A web-based system for collecting trial data will have programs designed to detect missing data or specific errors. If these errors are detected, a warning sign will be displayed next to coding boxes and a query will be generated. The investigator who receives the inquiry will correct the data after checking the original documents. Interim analyses will not be undertaken at any time during the whole period of study.

All principal investigators and research coordinators will have access to the cleaned final data sets. Project data sets will be housed at https://kiom1.mdsol.com/MedidataRave, and all data sets will be password protected.

### Monitoring

This study is an investigator-initiated trial, which explores the acupuncture mechanism and efficacy. A data monitoring committee (DMC) was not considered necessary in terms of safety concerns, outstanding benefits, and futility, as is often the case in similar studies.

The monitors, who are working in other independent divisions of the KIOM organization, will monitor source documents at all sites and will conduct at least one onsite-monitoring visit every 2 months. The monitors will review the source documents as needed, to determine whether the data reported in the Web-based system are complete and accurate. Source documents are defined as medical charts, associated reports, and records. The monitors will confirm that the regulatory binder is complete and that all associated documents are up to date. The regulatory binder should include the protocol and all revisions of informed consent, IRB approvals for all of the above documents, IRB correspondence, case report forms, and the investigator’s agreements.

## Discussion

To prevent or slow the progression of dementia, it is important to manage it in its early stage (i.e., the MCI state). Unfortunately, there are no recommended medications for MCI because cholinesterase inhibitors, well-known anti-dementia drugs, have more AEs than benefits when prescribed to patients with MCI [13–16]. In this situation, acupuncture therapy can help improve the cognitive function of patients with cognitive decline [19–24]. However, studies investigating the effects of acupuncture treatment in patients with MCI have compared acupuncture to conventional anti-dementia drugs (not sham acupuncture), and usually tested single acupoint stimulation, which is not commonly used in practice to treat patients. To assess the efficacy of acupuncture in MCI, we designed a randomized, assessor-blinded, sham-controlled trial. An acupuncture treatment protocol was developed through the consensus of investigators, to reflect actual practice.

Studies have identified abnormalities in the structure and function of the brain in patients with MCI compared to age-matched healthy adults [26, 54]. The association between progression of cognitive decline and MRI metrics including Aβ and Tau in the cerebrospinal fluid and gray matter volumes in the regions of the brain is known to play a role in cognitive function [55].

In this trial, we aim to investigate differences in functional brain responses to the WM task, functional brain networks, and brain structures following acupuncture treatment in patients with MCI. In order to clarify the efficacy of acupuncture, we will compare changes in MRI metrics between the acupuncture group and sham acupuncture group, and test whether improved cognitive function is associated with changes in MRI metrics following acupuncture treatment [54]. Although a few studies have investigated structural and functional brain plasticity in patients with MCI following acupuncture stimulation [25, 26, 56], to our knowledge, our study will be the first randomized sham-controlled trial reflecting actual practice (multiple acupoints and 24 treatment sessions) using MRI.

As described previously, we will especially focus on working memory, among different cognitive functions. Working memory deficits are already present in patients with MCI [57–59], and it is a predictor of negative prognosis [58]. In addition, working memory training can improve global cognitive functions in early AD [60]. Acupuncture can also affect working memory [61, 62]; thus, we expect that acupuncture treatment will improve cognitive function in MCI through improvement of working memory. Because our aim is to show the neural mechanism and the efficacy of acupuncture treatment, DST, not a measure of global cognitive function, has been selected as a primary outcome measurement. DST is commonly used to evaluate working memory [63]. A DST score will be obtained every 4 weeks to detect changes.

Cognitive decline in the elderly is also closely related to emotional problems such as depression and anxiety. In the depressive or anxious state, cognitive function declines and psychomotor retardation or agitation is observed. In MCI, high levels of depression and anxiety have an influence on the progression from MCI to dementia [12]. Thus, we will examine not only cognitive function but also the emotional state in participants with MCI. In addition, we will have a WM task fMRI run with emotional distractors and will then examine the brain responses to high arousal and negative valence pictures and the correlation between emotionally evoked brain responses and patients’ emotional rating scores.

The limitations of the study should be noted. We adopted Streitberger sham acupuncture as a control. The Streitberger sham needle has been designed for reliable control treatment in acupuncture research [64]. However, not only the Streitberger needle, but any type of sham acupuncture has limitations. First, we cannot blind the practitioner to the treatment allocation (our trial is not a double-blinded trial). The practitioner should be aware of the treatment type, and then they will push the shaft of needle into the handle for sham acupuncture as they were trained beforehand. In order to minimize the risk of bias as much as possible, we will carefully blind the participants and assessors to acupuncture type. Second, sham acupuncture often shows large non-specific effects [64–66] and produces physiological activity [67]. A non-specific effect of sham acupuncture cannot be dismissed in this trial, but we may compare the differences in neurological mechanisms between the two groups. Thus, we may identify the acupuncture-specific pathway associated with the improvement of cognition based on the MRI results even if the total (specific plus placebo) effect is not significantly different. Third, even if we wanted to consider MCID as a primary outcome, only MCIDs in the MMSE [68, 69] and Alzheimer’s Disease Assessment Scale-Cognitive Subscale (ADAS-Cog) [70, 71] for dementia have been studied. In those studies, the duration of interventions for neurocognitive disorders was much longer than in this trial. Thus, the MCID in the DST score for MCI cannot be included in this design. For establishing the MCID, it the acupuncture needs to be used for a longer period and interviews with participants or the Delphi expert consensus method are applied. Therefore, we calculated the effect size based on a previous study [29]. To our knowledge, there are several RCTs examining acupuncture for treatment of MCI [21], but Tan et al. [29] compared acupuncture to sham control and used the DST as an outcome measurement. Although the number of participants is small, it would be an appropriate reference to our study when considering clinical relevance. Finally, we have no healthy group as a control in this trial. A previous meta-analysis [72] showed differences between brain networks in MCI and healthy participants; however, our trial focuses on investigating acupuncture-induced functional and structural brain changes, not MCI-specific characteristics of brain function/structure relative to healthy controls. Thus, we will compare brain network changes between the acupuncture and sham acupuncture groups.

## Trial status

The study was registered with the Clinical Research Information Service on 25 May 2018, registration number KCT0002896. This protocol is based on version 3.2 of 6 March 2019. Recruitment of participants started on 8 June 2018 and the first participant was enrolled on 18 July 2018. Recruitment will continue until November 2019. The items from the World Health Organization Trial Registration Data set are summarized in Table 2.

**Table 2 Tab2:** The items from the World Health Organization Trial Registration Data Set

Data category	Information
Primary registry and trial identifying number	CRIS KCT0002896
Date of registration in primary registry	25 May 2018
Sponsor	KIOM
Contact for public/scientific queries	[name], KMD, Ph.D ([contact])
Public title	None
Scientific title	Neurocircuitry of Acupuncture Effect on Cognitive Improvement in Patients with Mild Cognitive Impairment Using Magnetic Resonance Imaging: A Study Protocol for a Randomized Controlled Trial
Countries of recruitment	Republic of Korea
Health condition(s) or problem(s) studied	MCI
Intervention(s)	Active comparator: acupuncture
	Sham comparator: non-penetrating sham acupuncture
Key inclusion and exclusion criteria	Ages eligible for study: 50–70 years; sexes eligible for study: both; accepts healthy volunteers: no
	Inclusion criteria: diagnosis of MCI, MoCA-K < 23, CDR score of 0.5, GDS grade 2–3
	Exclusion criteria: diagnosis of dementia, neurological disorders, mental disorders
Study type	Interventional
	Allocation: randomized; intervention model: parallel assignment; blinding: subject-assessor blinding
	Primary purpose: treatment
Date of first enrolment	18 July 2018
Target sample size	50
Recruitment status	Recruiting
Primary outcome(s)	DST
Key secondary outcomes	DSST, MoCA-K

*CRIS* Clinical Research Information Service, *DSST* Digit Symbol Substitution Test, *DST* Digit Span Test, *MCI* mild cognitive impairment, *MoCA-K* Korean version of Montreal Cognitive Assessment, *KIOM* Korean Institute of Oriental Medicine

## Data Availability

Not applicable.

## Abbreviations

AAN: American Academy of Neurology
AD: Alzheimer’s disease
ADAS-Cog: Alzheimer’s Disease Assessment Scale-Cognitive Subscale
AE: Adverse events
AFNI: Analysis of functional neuroimages
ANCOVA: Analysis of covariance
ANOVA: Analysis of variance
BDI-II: Beck Depression Inventory-II
BOLD: Blood oxygenation level-dependent
CDR: Clinical dementia rating
CDT: Clock drawing test
DARTEL: Diffeomorphic anatomical registration using exponentiated lie algebra
DSM-5: Diagnostic and statistical manual of mental disorder, fifth edition
DSST: Digit Symbol Substitution Test
DST: Digit Span Test
DTI: Diffusion tensor imaging
FAS: Full analysis set
FDR: False discovery rate
FDT: FMRIB software library’s diffusion toolbox
fMRI: Functional magnetic resonance imaging
FSL: FMRIB software library
GDS: Global Deterioration Scale
GLM: Generalized linear model
HIS: Hachinski Ischemic Score
IAPS: International Affective Picture System
IRB: Institutional Review Board
ITT: Intention-to-treat
K-CWST: Korean Color Word Stroop Test
K-ADL: Korean Barthel Activities of Daily Living
K-BNT: Korean Boston Naming Test
KHUGD: Kyung Hee University Hospital at Gangdong
KHUMC: Kyung Hee University Medical Center
K-IADL: Korean Instrumental Activities of Daily Living
KIOM: Korean Institute of Oriental Medicine
K-MMSE: Korean Mini Mental State Examination
K-WAB: Paradise Korean Western Aphasia Battery
MCI: Mild cognitive impairment
MCID: Minimal clinically important difference
MDD: Major depressive disorder
MNI: Montreal Neurological Institute
MoCA-K: Korean version of Montreal Cognitive Assessment
MRI: Magnetic resonance imaging
PP: Per-protocol
RCFT: Rey complex figure test
SAE: Serious adverse event
SD: Standard deviation
SGDS: Short Version of the Geriatric Depression Scale
SNSB-II: Seoul Neuropsychological Screening Battery-II
SPM: Statistical parametric mapping
STAI: State-Trait Anxiety Inventory
STRICTA: Standards for Reporting Interventions in Clinical Trials for Acupuncture
SVLT: Seoul Verbal Learning Test
TE: Echo time
TR: Repetition time
VBM: Voxel-based morphometry
VCIND: Vascular cognitive impairment, no dementia
WM: Working memory
